## Abstract

**Background:**

Given the world’s aging population, it is important to identify strategies that promote healthy cognitive aging and minimize cognitive decline. Currently, no curative pharmaceutical therapy exists for cognitive impairment and dementia. As a result, there is much interest in lifestyle approaches. Specifically, complex mental activity, such as cognitive training, may be a promising method to combat cognitive decline in older adults. As such, the industry of commercial computerized cognitive training (CCT) applications has rapidly grown in the last decade. However, the efficacy of these commercial products is largely not established. Moreover, exercise is a recognized strategy for promoting cognitive outcomes in older adults and may augment the efficacy of computerized cognitive training applications. Therefore, we propose a proof-of-concept randomized controlled trial (RCT) to examine the effect of a commercial CCT program in community-dwelling older adults.

**Methods:**

An 8-week RCT to examine the effect of a commercial CCT program, alone and preceded by a 15-min brisk walk, on cognitive function and explore the underlying neural mechanisms in adults aged 65–85 years old. Participants will be randomized to one of three intervention groups: 1) Computerized cognitive training (FBT); 2) A 15-min brisk walk followed by computerized cognitive training (Ex-FBT); or 3) A combination of educational classes, sham cognitive training, and balanced and tone exercises (active control, BAT). Participants in all intervention groups will attend three one-hour classes per week over the course of the intervention. Participants will be assessed at baseline, trial completion, and 1-year post study completion (1-year follow-up).

**Discussion:**

If results from this study show benefits for cognition at trial completion, CCT programs, alone or in combination with walking, might be a strategy to promote healthy cognitive aging in older adults. In addition, results from the 1-year follow-up measurement could provide important information regarding the long-term benefits of these CCT programs.

**Trial registration:**

ClinicalTrials.gov Protocol Registration System: NCT02564809; registered September 1, 2015.

## Background

The world’s population is aging, and the promotion of active aging is a global priority [1]. Cognitive impairment and dementia are now the leading cause of disablement and death in later life. The incidence of dementia is rising rapidly, and over 47 million people worldwide are diagnosed with dementia and this number is expected to triple by 2050 [1]. As an effective treatment or cure for dementia remains elusive, there are increased efforts to establish the efficacy of non-pharmaceutical strategies, such as targeted exercise training and cognitive training, on cognitive health in older adults. Even when an effective pharmacological therapy is available, lifestyle approaches (i.e., exercise, nutrition, and cognitive training) can be used as a complementary approach, as lifestyle interventions result in multidimensional benefits [2].

Interest in strategies such as cognitive training, a form of complex mental activities, has increased over the last decade. Tasks aimed to train for example executive functions, memory, or learning a language are considered complex mental activities, as long as they challenge an individual cognitively [3]. Improvements in cognitive function, such as episodic memory (e.g., delayed recall), were found in older adults who participated in videogames [4] or computer lessons [5]. Moreover, auditory perception training for 6 weeks, 1 h per day, resulted in improvements in problem solving and reasoning [6], which is considered to be positive far transfer. Thus, besides improvements in the trained domains, cognitive training could also show benefits of transfer [4, 6]. Aside from immediate benefits, the ACTIVE study [7] found that ten years post intervention, participants who received either speed-of-processing training or reasoning training for 5–6 weeks maintained effects of targeted cognitive abilities (i.e., speed-of-processing, reasoning). A meta-analysis of human cohort studies demonstrates that the amount of time involved in complex mental activities in early, mid- and late-life, was associated with a reduction in dementia incidence in later life [8]. Specifically, they found that increased complex mental activity in later life was associated with lower dementia rates, independent of other predictors, where more involvement in complex mental activities was found to lower dementia risk [8].

One example of complex mental activity that received increasing attention as a strategy to promote healthy cognitive aging is computerized cognitive training (CCT). The number of commercialized CCT programs has increased rapidly over the last years. A meta-analysis of CCT in older adults showed that CCT is able to improve overall cognitive function, memory (verbal, non-verbal), processing speed, working memory and visuospatial skills [9]. No improvements were found for executive functions and attention [9]. A recent randomized controlled trial (RCT) comparing multidomain CCT with an active control group found improvements in global cognition, memory and processing speed [10]. Improvements in memory and processing speed were maintained at 1-year follow up, indicating maintenance of CCT benefits [10]. Thus, CCT is a promising strategy to promote healthy cognitive aging, and is also a feasible strategy for those who are limited in their abilities to participate in other lifestyle strategies, such as exercise.

Aerobic exercise is a promising strategy to promote cognitive health, while benefiting cardiovascular function at the same time [11]. Research shows that aerobic exercise, such as walking, could benefit cognitive function such as executive functions (e.g., inhibition, processing speed), memory [11–14], as well as brain structure [13, 15] and function [16]. As both exercise and cognitive training are promising strategies to prevent or delay cognitive decline [17], perhaps by combining them the benefit may be increased. Importantly, whereas aerobic exercise can facilitate neuroplasticity by increasing the number of newly formed neurons, additional experience-dependent cognitive activity is necessary to promote synaptic plasticity and the survival and functional integration of the newly formed neurons into neural networks [18–21]. Moreover, due to the transient nature of the upregulation of neurotrophic factors [22] it has been suggested that cognitive training preferably takes place in temporal proximity to exercise training [23].

The objective of the current proof-of-concept RCT will be to examine the effect of CCT, alone and preceded by a 15-min brisk walk, on cognitive function and to explore the underlying neural mechanism in community dwelling older adults. Therefore, our aim is four-fold: 1) To compare the effects of an 8-week CCT program (i.e., Fit Brains***®*** Training: FBT), as well as the effects of a 15-min brisk walk prior to FBT (i.e., Ex-FBT), with an active control (i.e., Balanced And Toned, BAT) on cognitive performance in older adults aged 65–85 years old; 2) Using structural and functional Magnetic Resonance Imaging (MRI), to explore the effect of FBT and Ex-FBT compared with BAT on brain structure and function; 3) To explore whether the effects of FBT and Ex-FBT are moderated by baseline cognitive status (i.e., Mild Cognitive Impairment (MCI) versus non-MCI); 4) To explore whether Ex-FBT has additional benefits compared with FBT; and 5) To explore whether potential benefits from CCT are maintained at 1-year follow-up.

## Methods

### Trial design

vThis proof-of-concept RCT in community-dwelling older adults will have three experimental arms. We will include 120 community-dwelling adults aged 65–85 years old who will be randomized to one of three experimental groups: 1) Computerized cognitive training (FBT); 2) Exercise plus computerized cognitive training (Ex-FBT); or 3) Balanced and Toned (BAT, i.e., active control, see Fig. 1). There will be three measurement sessions: baseline, trial completion (i.e., 8 weeks), and 1-year follow-up. The study protocol follows the Consolidated Standard of Reporting Trials (CONSORT) statement [24] and basic requirements from the Standard Protocol Items: Recommendations for Interventional Trials (SPIRIT) [25]. The trial is registered at ClinicalTrials.gov (NCT02564809).

**Fig. 1 Fig1:**
[figure not shown]
Overview of participant flow

### Study setting

The study will be conducted at two locations in Metro Vancouver, BC (Canada): the Djavad Mowafaghian Centre for Brain Health at the University of British Columbia (UBC) and the Centre for Hip Health and Mobility at Vancouver General Hospital (VGH).

### Participants

Participants will be recruited from the community (Greater Vancouver, BC Canada) as well as through our database of previous research participants. Individuals showing interest in the study via advertisements in community centres or local newspapers will receive a short summary of the study and if still interested, will be screened over the telephone to determine eligibility. Participants from previous studies in our laboratory who expressed interest in future studies will be contacted either via mail or email.

### Eligibility

#### Inclusion criteria

For this study, we will include individuals who: 1) are aged between 65 and 85 years; 2) completed high school education; 3) live in their own home; 4) read, write, and speak English with acceptable visual and auditory acuity; 5) have preserved general cognitive function as indicated by a Mini-Mental State Examination [26] score of ≥24/30; 6) score > 6/8 on the Lawton and Brody Instrumental Activities of Daily Living Scale [27]; 7) are not expected to start or are stable on a fixed dose of anti-dementia medications (e.g., donepezil, galantamine, etc.) during the 8-week study period; 8) are able to walk independently; 9) are suitable to engage in 15 min of brisk walking based on the Physical Activity Readiness Questionnaire [28]; and 10) provide a personally signed and dated informed consent document indicating that the individual (or a legally acceptable representative) has been informed of all pertinent aspects of the study.

#### Exclusion criteria

We will exclude individuals who: 1) are diagnosed with dementia of any type; 2) are clinically suspected to have a neurodegenerative disease as the cause of MCI that is not AD, vascular dementia (VaD), or both (e.g. multiple sclerosis, Parkinson’s disease, Huntington’s disease, fronto-temporal dementia, etc.); 3) have clinically significant peripheral neuropathy or severe musculoskeletal or joint disease that impairs mobility, as determined by his/her family physician; 4) are taking medications that may negatively affect cognitive function, such as anticholinergics, including agents with pronounced anticholinergic properties (e.g., amitriptyline), major tranquilizers (i.e., typical and atypical antipsychotics), and anticonvulsants (e.g., gabapentin, valproic acid, etc.); and 5) are planning to participate, or already enrolled in, a concurrent clinical drug trial.

A subset of participants will undergo MRI scanning. For this MRI subset, we will exclude individuals who do not meet the specific scanning requirements of the UBC MRI Research Centre. Specifically, we will exclude anyone with: pacemaker, brain aneurysm clip, cochlear implant, surgery or tattoos within the past 6 weeks, electrical stimulator for nerves or bones, implanted infusion pump, history of any eye injury involving metal fragments, artificial heart valve, orthopedic hardware, other metallic prostheses, coil, catheter or filter in any blood vessel, ear or eye implant, bullets, or other metallic fragments.

### Classification by baseline cognitive status

To explore whether the intervention effects (i.e., FBT and Ex-FBT) are moderated by baseline cognitive status, we will classify individuals based on their baseline Montreal Cognitive Assessment (MoCA) [29]. The MoCA is a 30-point test that covers multiple cognitive domains [29]. The MoCA has been found to have good internal consistency and test-retest reliability and was able to correctly identify 90% of a large sample of individuals with MCI from two different clinics [29]. Thus, participants with a baseline MoCA score ≤ 26/30 will be classified as probable MCI and those with a MoCA score > 26/30 will be classified as cognitively normal.

### Interventions

For the 8-week intervention period, all participants will be asked to come to the study location (i.e., VGH or UBC) 3 times per week for 1 h. Thus, all participants will attend 24 1-hour classes at VGH or UBC. These classes will have a set time, and thus after randomization participants will come in on Monday, Wednesday and Friday at the same time each day. Over the course of the four study cohorts, group times will be kept consistent (+/− 15 min). In addition, study staff will be kept consistent over all four cohorts to ensure training consistency. Depending on group size, students/staff will help facilitate study classes to meet the participants’ needs.

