#### Balanced and toned (BAT)

Participants randomized to the BAT group will be required to attend 3 formal 1-h training sessions per week, for 8 weeks, at the Djavad Mowafaghian Centre for Brain Health (UBC) and/or the Centre for Hip Health and Mobility (VGH). Specifically, the BAT participants will complete a total of 8 h of sham cognitive training, 8 h of sham exercise training, and 8 h of education regarding brain health over the 8-week training.

We have largely designed the sham cognitive training of the BAT protocol based on the work of Baniqued and colleagues [34] who examined the nature of cognitive abilities tapped by casual online games. They identified online games that largely tapped solely into visuo-motor speed, such as Alphattack and Crashdown. Alphattack requires players to prevent bombs from landing by pressing the character specified by the approaching bomb (source: miniclip.com). Crashdown requires players to prevent the wall from reaching the top of the display by clipping on three or more adjacent same-coloured bricks to remove them (source: miniclip.com). As these online games do not significantly tap into memory abilities, we use similar online games in our BAT protocol. In addition to exercises on the iPad we include group-based games, such as drawing using both their dominant and non-dominant hand, writing captions on cartoons, and word games.

The exercise component of the BAT program will consist of once weekly balance and tone classes. The exercise program will be led by certified fitness instructors (i.e., CPR certified and NCAA certified or equivalent) and includes stretching exercises, range of motion exercises, basic core-strength exercises including kegals (i.e., exercises to strengthen the pelvic floor muscles), balance exercises and relaxation techniques. Key balance exercises include Tai Chi-based forms (i.e., Crane, Tree Pose), tandem stand, tandem walking, and single leg stance (eyes open and closed). Previous use of this protocol showed no improvements of cognitive functioning as a result of the BAT program [35]. These sessions will be held at the Centre for Hip Health and Mobility.

Additionally, once a week the participants will attend educational classes. For the first four 1-hour education sessions, participants will attend lectures relating to brain health, such as sleep and goal setting. During the remaining four weeks, participants will create their individual photo book using the iPad.

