### Statistical analysis

#### Effects of CCT

The primary and secondary outcomes will be analyzed using an identical analytic model, which will follow the intention-to-treat principle, such that all randomized participants will be included to estimate treatment effects irrespective of deviations from treatment protocol (e.g., loss to follow-up, non-compliance). This will be done using linear mixed models using maximum likelihood estimation. The model will include random intercepts, and fixed effects of time (baseline, trial completion), intervention assignment (FBT, Ex-FBT, BAT), and their interaction. Baseline MoCA score and age will also be included as fixed effect covariates. Treatment effects will be indicated by a statistically significant treatment by time interaction. Two planned simple contrasts will be performed to assess differences in changes in the primary and secondary outcomes between: 1) the FBT group and the BAT group; and 2) the ex-FBT group and the BAT group. A secondary planned contrast will determine whether FBT and ex-FBT will differ in changes in the primary and secondary outcomes over time. To explore maintenance of treatment effects, we will perform repeated measures with linear mixed models using maximum likelihood estimation. The models will include random intercepts, and fixed effects of time (baseline, trial completion, 1-year follow up), intervention assignment, and their interaction. Baseline MoCA score and age will also be included as fixed effect covariates.

Follow-up sensitivity analyses will restrict the study sample to individuals with valid data at all three time points (baseline, trial completion, and 1-year follow-up). The same linear mixed models describe above will be employed to determine whether inferences will be similar for the intention-to-treat and complete-case study samples.

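### Every arm is taught in arm-specific classes, but the listed model has no class effect on change, so the standard errors of both primary contrasts are too small if classes differ

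*Protocol article*

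**What the plan says.** Under Interventions, the protocol article states that "all participants will attend 24 1-hour classes at VGH or UBC", and that "after randomization participants will come in on Monday, Wednesday and Friday at the same time each day". Delivery is spread over four cohorts: "Over the course of the four study cohorts, group times will be kept consistent". Two sentences there bear on how alike the classes will be: "study staff will be kept consistent over all four cohorts to ensure training consistency", and "Depending on group size, students/staff will help facilitate study classes".

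The arm subsections give each arm its own session content, so a class holds participants of one arm only. FBT and Ex-FBT train on the iPad and add three home sessions a week. BAT has weekly instructor-led exercise, weekly education classes and sham training of which the article says "In addition to exercises on the iPad we include group-based games". No home training is described for BAT.

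Under Effects of CCT, "The model will include random intercepts, and fixed effects of time (baseline, trial completion), intervention assignment (FBT, Ex-FBT, BAT), and their interaction". Baseline MoCA and age are the only covariates. The level of the random intercepts is not named; with repeated measures it reads as the participant. The one-year model has the same structure. Under Sample size and randomization, the trial is sized from an SD of 1.1 with no allowance for clustering.

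**The concern.** The treatment effect is the time-by-arm interaction, that is, a difference between arms in mean change. A participant random intercept absorbs stable differences between people and drops out of change. It cannot absorb something that moves a whole class between baseline and week 8, such as peers, group size, extra helpers, or the season for the outdoor walks in Ex-FBT. With each class nested in one arm, that shared movement adds to the variance of the arm mean, while the model computes its standard error as if all participants were independent.

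At stake is the error rate of the two primary contrasts: a benefit of computerized training over BAT could be declared too easily. BAT is the comparator in both, so a class effect in BAT enters both. Because the article lists the model in full, this is something it fixes and not merely a detail left open.

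**Working it through.** **Inputs from the article.** Four cohorts; three arms, 1:1:1, block size 12; 36 participants (read as per arm) for power 0.80, SD 1.1, alpha 0.05 (taken as two-sided), 10% dropout; predicted mean changes 0.31 (FBT), 0.40 (Ex-FBT), −0.31 (BAT).

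**Assumptions not in the article.** One class per arm per cohort, so 4 × 3 = 12 classes with 36/4 = 9 completers each. The ICC of change within class is unknown, so a range is used.

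**The article's own figure.** For Ex-FBT–BAT the difference is 0.40 + 0.31 = 0.71, and n = 2 × (1.96 + 0.842)² × 1.1² / 0.71² ≈ 38 per arm, with power 0.78 at 36. That is close to the stated 36. For FBT–BAT the difference is 0.62, which needs 50 per arm; power at 36 is about 0.66. Dropout: 36/0.9 = 40 per arm, 120 in total. No clustering term enters, and there is no spare power to absorb one.

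**Effect of class variation.** Design effect DE = 1 + (9 − 1) × ICC. The true standard error is √DE times the modelled one. Actual error of the nominal 5% test = 2 × [1 − Φ(1.96/√DE)].

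| ICC | DE | √DE | Actual error | Effective n per arm (36/DE) |
|---|---|---|---|---|
| 0 | 1.00 | 1.00 | 5.0% | 36 |
| 0.01 | 1.08 | 1.04 | 5.9% | 33 |
| 0.02 | 1.16 | 1.08 | 6.9% | 31 |
| 0.05 | 1.40 | 1.18 | 9.8% | 26 |

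Simulating 40,000 trials of 4 cohorts × 3 arms × 9 participants and ignoring class gave 5.8%, 6.8% and 9.8% at ICC 0.01, 0.02 and 0.05.

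**Milder assumptions.**
- Clustering in BAT only: the contrast variance is inflated by (1 + DE)/2, that is 1.04, 1.08 and 1.20, giving errors of 5.5%, 5.9% and 7.4%.
- Classes of 5 in all arms at ICC 0.05: DE = 1 + 4 × 0.05 = 1.20, again 7.4%.

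**Cohort effects common to all arms.** With arms near-balanced within cohorts, such an effect cancels from the contrasts. Simulated error when it is left out is 4.5% at a cohort ICC of 0.05 and 4.3% at 0.10, slightly conservative. Adding cohort fixed effects when the variation is class-specific does not lower the error: 6.1%, 7.0% and 10.1% at class ICC 0.01, 0.02 and 0.05, against 6.1%, 6.9% and 9.8% without them in the same simulation.

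**What a class-level analysis can do.** Comparing class means on 12 − 3 = 9 degrees of freedom held the error at 5.0–5.2% in 20,000 simulated trials. Power for FBT–BAT at ICC 0: the standard error is 1.1 × √(2/36) = 0.259 and the non-centrality 0.62/0.259 = 2.39. That gives power 0.57 on 9 df (critical t 2.26), 0.52 on 6 df if cohort terms are added (critical t 2.45), and 0.66 for the participant-level test. The estimated class variance falls to zero in about 42–46% of trials at ICC 0.02 and 27–33% at ICC 0.05.

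**The case against.** The strongest reply is that clustering may be negligible here. The article keeps staff the same across cohorts, so staff are a poor candidate for differences between classes. Fit Brains training is done on an iPad and adapts to each person's performance, and half of the 48 FBT hours are at home. Group games, instructor-led exercise and lectures are described only for BAT. Two locations may mean more and smaller classes. At ICC 0 there is no defect. All of this stands. It points to a small ICC and is why the upper end of the range should not be read as a forecast. It does not remove peers, group size, helpers that vary with group size, or season, and BAT has no described home training to dilute a class effect.

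It may also be said that this is a proof-of-concept trial, that an article may leave sensitivity analyses to an analysis plan, and that 12 classes are too few to estimate a class variance well. The first two limit the weight of the point. The third is right, and it rules out a class-level primary test, but not a supporting analysis that reports its own uncertainty.

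A reader might infer that the missing cohort term is itself the fault, or that adding one would repair it. The article does not support that: blocked 1:1:1 allocation nearly balances the arms within cohorts, and the check shows that the term neither causes nor cures the inflation.

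**Conclusion.** The point holds conditionally. Classes are arm-specific and the listed model leaves out any class effect on change, so any such effect makes the standard errors of both primary contrasts too small. Under the assumed 12 classes of 9 with equal ICC, the actual error is about 5%, 6%, 7% and 10% at ICC 0, 0.01, 0.02 and 0.05. It is about 7.4% at ICC 0.05 if classes hold 5, or if clustering is confined to BAT. The ICC, class size and number of classes are assumptions; only the four cohorts, three arms and 36 per arm come from the article.

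A reader might go further and infer that the primary test is invalid or that its error will be near 10%. The article gives no figure from which that follows, and its delivery features suggest a smaller effect. A sensitivity analysis is warranted; a change of primary test or of sample size is not shown to be needed.

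**What to change.** Keep the stated primary model. Pre-specify a sensitivity analysis of the FBT–BAT and Ex-FBT–BAT contrasts that allows for class, in one of two forms:
- add a random class (cohort by arm) effect on the change from baseline, fitted by REML with small-sample degrees of freedom; or
- compare class means of change, using the between-class variance (9 df with 12 classes).

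Report the class variance with its uncertainty, the number and size of classes, and whether the primary conclusion holds. Cohort and cohort-by-time terms are optional for precision. If they enter the class-level analysis, they reduce it from 9 to 6 df.

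The cost is a little analysis work and a record of class membership. The article says attendance is recorded; membership should follow from cohort and arm, plus site and time slot if an arm has several classes. The downside is a wider interval and lower power (0.57, or 0.52 with cohort terms, against 0.66 for FBT–BAT at ICC 0). A class variance estimated at zero will also be common, and should not be read as proof that classes do not differ.
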